## Abstract

**Background:**

Low back pain (LBP) is one of the most disabling diseases and a major health issue. Despite the evidence of a link between paraspinal and gluteal muscle dysfunction and LBP, it is unknown whether aquatic exercises can lead to improvements in paraspinal and gluteal muscle morphology and function, and whether improvements in overall muscle health are associated with improvements in patients’ outcomes. The unique properties of water allow a water-based exercise program to be tailored to the needs of those suffering from LBP. This study uses magnetic resonance imaging (MRI) to investigate the effect of an aquatic exercise program versus standard exercise on 1) paraspinal and gluteal muscle size, quality and strength and 2) pain, disability, and psychological factors (pain related fear, depression, anxiety, sleep quality) in chronic LBP.

**Methods:**

This study will include 34 participants with chronic non-specific LBP and moderate to severe disability, aged between 18 and 65, who will be randomly assigned (1:1) to the aquatic exercise group or land-based standard care exercise group. Both groups will receive 20 supervised sessions, twice per week over 10 weeks. MRIs will be obtained along the lumbosacral spine (L1-L5) and pelvis at the start and end of the intervention to assess the effect of each exercise intervention on paraspinal and gluteal muscle size and quality. Pre- to post-intervention changes in all outcomes between each group will be assessed, and the association between the changes in back muscle quality and clinical outcomes will be examined. Between-subjects repeated measure analysis of variance will be used to examine the changes in paraspinal muscle morphology over the different time points. Linear mixed models will be used to assess whether baseline scores can modify the response to the exercise therapy treatment.

**Discussion:**

This study will determine if water-based exercises targeting the lower back and gluteal muscles can lead to important changes in muscle quality and function, and their possible relation with patients’ pain and functional improvements. Our findings will have strong clinical implications and provide preliminary data to design a community program to better support individuals with chronic LBP.

**Trial registration:**

NCT05823857, registered prospectively on April 27^th^, 2023.

**Supplementary Information:**

The online version contains supplementary material available at 10.1186/s12891-023-07034-0.

## Background

Low back pain (LBP) is a well-recognized and significant public health concern [1, 2]. The healthcare-related cost for chronic LBP and social consequences are substantial for the society [2, 3]. In Canada, LBP related medical costs range between 6 and 12 billion dollars each year, and continue to increase [4]. In addition, impairments in strength [5, 6], flexibility [7, 8], endurance [9], and obesity [10] are well documented in individuals with chronic LBP. Exercise therapy is currently the most widely used form of conservative treatment for chronic LBP, with recent reviews supporting its effectiveness [11, 12]. Therefore, exercise therapy is recommended as a first-line treatment for people with chronic LBP [13], especially for the improvement of pain, quality of life, depression and disability/functional status [13–21]. Given the body of evidence linking paraspinal muscle morphological changes (e.g. atrophy, fatty infiltration, asymmetry), gluteal functional changes (e.g., decreases in strength and muscle activation) [22–24] and LBP [25, 26], and lack of spinal stability due to impairments in the trunk and paraspinal muscles [27], many exercise interventions focus on activating of these muscles [17–19].

However, it is difficult for those with LBP to perform strengthening exercises without avoiding the weight load on their spine [28]. In addition, fear avoidance beliefs which refer to fear of physical movement and work activities that may elicit pain is very common in individuals with chronic LBP [11, 12]. One form of exercise that has been suggested as a promising and safer treatment alternative for individuals with LBP is aquatic exercise, with less risk of injury and difficulty performing exercises [14, 29–35]. Water immersion decreases axial loading of the spine and, through the effects of buoyancy, allows the execution of movements that are usually difficult to perform on land by reducing stress in joints [36, 37]. The unique properties of water, such as buoyancy, allow a water-based exercise program to be tailored to the needs of those suffering from LBP. Aquatic exercise may improve pain and disability [38], and maintain quality of life in individuals with chronic LBP [35], especially in individuals with low levels of physical fitness [39, 40]. Improvements in muscle strength [41] and cardiovascular fitness [31, 42] through continuous limb movements against water resistance have been reported as well. A recent systematic review and meta-analysis on the effect of aquatic therapy in LBP, showed that this may not only be an effective alternative to conventional LBP treatments, but also a safe and enjoyable substitute to improve physical function [38]. These findings suggest the potential benefits of aquatic exercise for individuals with chronic LBP.

Recent reviews concluded there is no clear particular form of exercise that is more effective than others [17–19]. Interestingly, when comparing aquatic therapy to land-based exercise in individuals with chronic LBP, some study results have showed no significant differences in decreased pain levels or improved functional ability between the two exercise types [31, 34]. However, one study showed better improvements in functional ability in the aquatic therapy group compared to the land-based exercise group [35]. Moreover, Psych et al. showed that aquatic therapy produced comparable back and gluteal muscle activation and intensity to land-based exercise [43]. Overall, there are some inconsistencies between studies comparing aquatic therapy to land-based exercise in individuals with chronic LBP.

While many exercise intervention studies reported improvements in patient-reported outcomes such as pain, physical function, and depression, few comprehensive imaging studies have examined these outcomes in relation to muscle morphology (e.g. hypertrophy, fatty infiltration) and functional improvements (e.g. strength, endurance, contraction), and many have been critiqued for their low quality and high potential of methodological bias [44]. Furthermore, we are not aware of any imaging studies that have specifically assessed the effect of aquatic therapy on paraspinal and gluteal muscles morphology and function. Lastly, while mobile health applications to manage LBP have been used in the past, it remains unclear if they are feasible to use both in a standard clinical setting and during a specific LBP exercise intervention. Most previous studies have used such applications as a stand-alone intervention. Interestingly, a randomized controlled trial (RCT) investigated the efficacy of a stand-alone mobile-Web intervention to help users adopt self-management strategies for non-specific LBP [45]. This tool was effective in the prevention and management of LBP occurrences, on current back pain, behavioral, and worksite outcomes, by tailoring content to users’ preferences and interests. Another study showed that an iPad application screening for pain contributors and providing personalized education for older adults with chronic LBP, had highly rated usability and utility [46]. These studies support the potential value a technological intervention has in this population, and could possibly be applied in clinical settings to educate patients about LBP, to facilitate patient-provider communication for personalized treatment strategies, and enhance compliance. The application “play the pain” was specifically developed for subjects dealing with chronic pain, however, it has not been used or tested in a clinical population (e.g., chronic LBP) to date. Therefore, the purpose of this study is to investigate the effect of an aquatic therapy exercise program versus standard care on 1) paraspinal and gluteal muscle size, composition (e.g. fatty infiltration) and strength, 2) pain, disability, quality of life, and psychosocial factors (e.g. kinesiophobia, catastrophizing, anxiety, and depression) in individuals with chronic LBP, and 3) to evaluate the feasibility, adherence and satisfaction of participants to use the “play the pain” app to track their pain levels and the activities they used to cope with the pain.

### Hypotheses

It is hypothesized that participants in the aquatic therapy group will show a significant improvement in 1a) paraspinal and gluteal muscle size and 1b) paraspinal and gluteal strength following the intervention, as compared to the standard care group. We also hypothesized that both groups will show improvements in pain, disability, quality of life, and psychosocial factors following the completion of the intervention, however the effects will be greater in the aquatic group as compared to the standard care group. Finally, we hypothesized that it will be feasible to implement the app in both the standard care and aquatic exercise groups, and that participants will be compliant and satisfied with the application.

## Methods/design

### Study design

This will be a two-arm prospective RCT. This protocol was reported in accordance with the SPIRIT guidelines [47] and CERT recommendation for Exercise Interventional Trials [48].

### Study setting

This study will be conducted at the Concordia University School of Health, Montreal, Canada (NCT05823857). The proposed project was approved by the Central Ethics Research Committee of the Quebec Minister of Health and Social Services (# CCER-21–22-35). All participants will sign a consent form prior to beginning the study.

### Participant recruitment

Study participants will be recruited from the School of Health Athletic Therapy clinic in Montreal, Canada and through poster and media advertising (e.g. email blast by the School of Health) as this has been shown to be an effective manner to attract participants [49]. If individuals’ express interest in participating in the trial, a member of the research team will contact them to discuss the study further, interview them, confirm eligibility, obtain consent, and enroll participants.

### Participants

#### Inclusion criteria

Individuals will be eligible to participate in the trial if they meet the following criteria:Chronic non-specific LBP (> 3 months), defined as pain in the region between the lower ribs and gluteal folds, with or without leg pain.Currently seeking care for LBP.Aged between 18 to 65 years old.English or French speakersHave a score of “moderate” or “severe” disability on the modified Oswestry Low Back Pain QuestionnaireDo not currently engage in sports or fitness training specifically for the lower back muscles (3 months prior the beginning of the trial).

#### Exclusion criteria

Participants will be excluded if they meet one of the following criteria:Evidence of nerve root compression or reflex motor signs deficits (e.g., weakness, reflex changes, or sensory loss with same spinal nerve),Previous spinal surgery or vertebral fractures,Other major lumbar spine structural abnormalities (e.g., spondylolysis, spondylolisthesis, or lumbar scoliosis > 10°)Comorbid health conditions that would prevent active participation in exercise programs (e.g. screened with Physical Activity Readiness Questionnaire)

### Randomization

After providing written informed consent, participants will be randomly assigned to treatment groups (1:1) using consecutively numbered sealed opaque envelopes (e.g., computer-generated randomization sequence with permuted blocks) created by an individual not involved in the study.

### Blinding

Since blinding of therapists and participants is generally not possible in exercise intervention trials [50], only the assessor will be blinded.

### Procedure

Eligible participants will be randomized into an aquatic therapy group or land-based standard care group. The intervention period will last 10 weeks, with a frequency of 2 times a week for each group at the School of Health, Concordia University. This frequency of training is in accordance with previous related exercise intervention studies for chronic LBP [19]. The duration of 10 weeks was chosen as strength improvements from training largely occur within that time period [51]. All methods will be carried out in accordance with relevant institutional guidelines and regulations. Written consent form will be obtained from all participants prior any data collection, and will be obtained to publish this paper.

### Swim ex water-based trunk stabilization group (Swim Ex)

Participants in this group will perform trunk stabilization, which will be based on a variety of aquatic exercises in different positions, intended to activate the multifidus and transverse abdominis in a co-contraction. Additionally, hip and gluteal specific exercises will be completed to promote strengthening of the gluteus maximus, gluteus medius, and gluteus minimus muscles. The aim of these exercises is to enhance the strength and dynamic stability of the spine and its surrounding musculature in a functional and yet non-weight-bearing way. Each exercise will be performed 10 times while sustaining the muscles co-contraction for 5–10 s and will be progressed gradually by adding low load to the muscles by means of external leverage at the limbs (discs, hand paddles), resistance material (kickboard, dumbbell floats), water current and/or leg length, and by gradually adding repetitions. Each training session (~ 60 min) will be privately supervised one-on-one by a certified Athletic Therapist (AT) and take place in the School of Health AT Clinic/Swim Ex pool. The level of difficulty will be increased using the Borg Rating of Perceived Exertion Scale (1–10 scale) (e.g. set level three = moderate or four = somewhat hard) and the Category Ratio scale (0–10 pain scale) [52]. This aquatic exercise program (refer to Table 1) was adapted from a recent study in adults with chronic LBP [43].

**Table 1 Tab1:** Aquatic exercise program group

	**Aquatic Exercises**	**Volume**	
**Warm-Up** (10 min)	**Water walking:** forwards, backwards, sideways—left and right. Progressively increase walking speed	3 min (30 s / direction)	
	**Small hops:** feet shoulder width apart, squat, then jump and bring feet close together and squat back down	1 min (30 s/ direction)	
	**Leg kicks:** kick front, kick out by side, kick back	1 min (30 s / leg)	
	**Marching:** raise knees, heel to buttocks—as tolerated	2 min (1 min each)	
	**Horizontal kicking:** on stomach, while holding onto edge of pool, kick legs and try to maintain body horizontal. Use floating device under the waist to modify difficutly	1 min (30 s each)	
	**Upper body oscillations:** Moving both arms in an oscillatory fashion from in front of you to out by your side	1 min	
	**Bow and Arrow:** rotate the torso by bringing your arms close to your body as if you’re shooting a bow and arrow. Alternate sides	1 min	
**Training** **Session** (​​40 min)	**Multi-directional Lunges:** forward, backward, sideways lunges back and forth	2 sets × 10 repetitions / direction	
	**Squats:** Place both arms by your side. Bend down in a squat position and then return to starting position. Can control speed of exercise done to make it harder	2 sets × 1 – 2 min	
	**Step-Ups:** Using an underwater step, place one foot on the step with hands on your waist and transfer weight to step up	2 sets × 8—12 repetitions / side	
	**Single leg squat:** Stand on one leg with both arms by your side. Perform the single leg squat until the knee moves in front of the toes. Remove hand support to increase difficulty	2 sets × 8 – 12 repetitions / side	
	**Standing Hip Abduction:** Stand on one leg, while either maintaining your balance or holding on to the side of the pool. Bring the leg that you aren’t standing on outwards as far as possible as long as the movement comes your hip. Use an elastic band above the ankles to make the exercise harder	2 sets × 10 repetitions / side	
	**Standing Hip Extension:** Stand on one leg, while either maintaining your balance or holding on to the side of the pool. Bring the leg that you aren’t standing on behind you as far as possible as long as the movement is only coming from your hip. Use an elastic band above the ankles to make the exercise harder	2 sets × 10 repetitions / side	
	**Concentric chest press + row:** Lunge or squat down to chest-deep water and hold dumbbell floats vertically between hands with arms fully outstretched in front just below the water surface. Pull dumbbell floats close to the chest (bringing arms backwards towards body) and then push forwards to starting position, while staying put	2 sets × 1—3 min	
	**Underwater punches:** Lunge down to have your arms just below the water surface, with one arm fully outstretched in front and the other close to body. Holding Aqualogix dumbbells, perform alternate punching with each arm	2 sets × 1 – 3 min repetitions	
	**Concentric Shoulder Flexion + Shoulder Extension:** Place one arm by side and the other outstretched in front just below water surface with palms facing direction of movement. Alternately bring one arm upwards just below the water surface while bringing the other arm to the side. Use hand paddles to increase resistance and change the front leg between sets	2 sets × 10—20 repetitions	
	**Knee Raises:** Hold the aquatic dumbbell in each hand with arms by sides while in a seated position. Raise one knee until thigh is parallel to the surface of the water. Alternate legs	2 × 10—20 repetitions	
	**Horizontal Woodchopper:** Have your hands with your arms fully outstretched in front just below water surface. Rotate your torso gradually as far to one side as possible and then back to the midline. Alternately do the same with other side	2 sets × 10—20 repetitions / side	
	**Diagonal Woodchopper:** Have your hands with your arms fully outstretched in front just below water surface. Rotate your torso gradually as far to one side as possible while bringing the hands down diagonally and then back to the midline. Alternately do the same with other side	2 sets × 10 – 20 repetitions / side	
	**Water Ab Rollout:** Start in upright posture with arms outstretched in front of you and your hands resting on the surface holding dumbbell floats. Slowly move the dumbbell floats forwards while keeping your body in a neutral posture tilting on the tips of the toes, and then return to starting position. You should feel the movement working your abdominal muscles	2 sets × 10—15 repetitions	
**Cool-Down** (10 min)	**Free water-activity:** walking, standing, swimming	1 min	
	**Stretching / Mobility exercises:** Hip CARs (controlled articular rotations)	2—5 × each leg	
	**Stretching/Mobility exercises:** Standing quad stretch	2 × 30 s per muscle group	
	**Stretching/Mobility exercises:** Standing hamstring stretch (extend leg + lean in)	2 × 30 s per muscle group	
	**Stretching/Mobility exercises:** Anterior chain stretch: grab arms behind back + open up chest	2 × 30 s per muscle group	
	**Stretching/Mobility exercises:** Seated Fig. 4 stretch	2 × 30 s per muscle group	
	**Stretching/Mobility exercises:** Standing open book (hold onto side of pool, lift leg + rotate away)	2 × 30 s per muscle group	
	**Relaxation:** Lay on your back with a noodle supporting you under your waist and occiput and take deep breaths	1 – 5 min	

Exercise will progress over the weeks by adding resistance to certain exercises (water current, ankle weights, hand paddles, dumbbell floats, kickboards, resistance bands, discs), as well as increasing in the number of repetitions

### Standard care group

Participants in this group will receive the standard LBP treatment in the School of Health Athletic Therapy clinic and will be privately supervised one-on-one by a certified AT who will be conducting the sessions. The AT will complete a thorough assessment of the eligible participants with chronic LBP and administer a range of interventions including stretching, strengthening and stabilization exercise, aerobic conditioning, and manual mobilization techniques. No attempt will be made to try to regulate/standardize the treatment received, however information about pain medication and co-interventions will be collected throughout the duration of the study.

### Data collection

All outcomes will be obtained at baseline for both intervention groups. All baseline assessments (e.g. MRI, strength, questionnaires) will be repeated at the end of the intervention during a 10-week follow-up (refer to Table S1 in Appendix). All self-reported questionnaires will be completed in-person using paper forms. Imaging outcomes (e.g., MRI) and lumbar extensor muscle assessments (e.g., strength) will be acquired at the School of Health, Concordia University. Demographic characteristics will be acquired via a self-reported questionnaire at baseline, after randomization.

### Outcome measures

#### Primary outcome measure

Multifidus muscle size and composition (e.g., fatty infiltration).

##### MRI assessment of multifidus muscle morphology

All participants will undergo baseline routine lumbosacral MRI evaluation prior the beginning of the exercise intervention using the School of Health’s 3-T General Electric (Chicago, IL, USA) MRI machine. Axial T2-weighted and IDEAL (Lava-flex, 2 echo sequence) will be obtained from L1 to L5 to assess the multifidus morphology and composition. Bilateral manual segmentation of regions of interest (ROI) representing the cross-sectional area (CSA) of the multifidus muscle will be acquired on axial T2-weighted slices from the most cranial aspect of the first lumbar vertebra (L1) to the most caudal aspect of the fifth vertebra (L5) to calculate the summative 3D volume of the right and left side at each level (more accurate assessment than single slice). IDEAL axial water and fat images will be used to calculate the percent fat-signal fraction: %FSF = (Signal_fat_/[Signal_water_ + Signal_Fat_] × 100) of the muscle. The Horos DICOM viewer software will be used for imaging analysis.

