##### MRI assessment of erector spinae and gluteal muscles morphology

The same method, as described above for the multifidus muscle, will be used to assess the erector spinae morphology and composition at each lumbar level. Similarly, a routine pelvic MRI T2-weighted and IDEAL (Lava-flex, 2 echo sequence) will also be acquired to assess gluteus maximus, gluteus medius and gluteus minimus muscle size and composition. IDEAL axial water and fat images will be used to calculate the percent fat-signal fraction: %FSF = (Signal_fat_/[Signal_water_ + Signal_Fat_] × 100) of each muscle. The Horos DICOM viewer software will be used for imaging analysis.

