### Sample size justification

While the effect aquatic therapy on paraspinal and gluteal muscles morphology and composition has never been investigated in chronic LBP, previous studies [35, 75, 76], showed significant improvement in multifidus muscle cross-sectional area (CSA) following other exercise interventions with medium to large effect sizes. Based on these studies, we used a mean effect size of 0.73 to calculate our sample size at a level of confidence of 0.05 and 80% power. Accordingly, a sample size of 17 participants in each group will be recruited.

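### Per-level muscle volume depends on how many slices fall inside each vertebral level; mean cross-sectional area per level would remove most of that noise at no cost (minor, precision only)

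*Protocol article*

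**What the plan says.** The primary outcome (Primary outcome measure) is "Multifidus muscle size and composition (e.g., fatty infiltration"), so it has a size part and a composition part. Under MRI assessment of multifidus muscle morphology, the muscle is outlined by hand on axial T2-weighted slices "from the most cranial aspect of the first lumbar vertebra (L1) to the most caudal aspect of the fifth vertebra (L5"), and the areas are used "to calculate the summative 3D volume of the right and left side at each level (more accurate assessment than single slice"). Composition is handled differently: "IDEAL axial water and fat images will be used to calculate the percent fat-signal fraction", which is a signal ratio.

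For the erector spinae, "The same method, as described above for the multifidus muscle, will be used to assess the erector spinae morphology and composition at each lumbar level". The comparison is between two scans, since "All baseline assessments (e.g. MRI, strength, questionnaires) will be repeated at the end of the intervention during a 10-week follow-up" (Data collection).

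The Sample size justification takes its effect size of 0.73 from studies that "showed significant improvement in multifidus muscle cross-sectional area (CSA) following other exercise interventions", and arrives at 17 per group with 80% power.

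**The concern.** A summed volume is slice spacing times the sum of the traced areas. At a muscle's natural ends the area tapers to zero and one slice more or less hardly matters. At a vertebral border the area is far from zero, so each slice counted in or out carries a full slice of muscle.

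Whether a slice centre falls just inside or just outside a border depends on where the slice grid sits on that day. The bony height of a level is fixed over 10 weeks, so a within-participant difference in slice count carries no information about the muscle, yet the summed volume records it as a change. At stake is the precision of per-level size change: in the group comparison, and in the regressions of symptom change on muscle change, where noise in the muscle measure pulls slopes toward zero.

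**Working it through.** **The plan's own figure.** With d = 0.73, two-sided alpha 0.05 and 80% power, a paired t-test (noncentral t) needs n = 17 (power 0.807). A two-sample t-test has power 0.542 at 17 per group. The choice between these bases is a separate matter; both are carried below only to show the effect of added noise.

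**Inputs.** From the article: per-level summation, landmark limits, two scans, d = 0.73, 17 per group. Assumed, because not given: spacing s = 3–5 mm, level height L = 30–40 mm, L1–L5 length 170–190 mm, and a slice-grid position that varies freely between visits.

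**Chance that the count differs.** A level of height L holds either the whole-number part of L/s slices or one more. With f the fractional part of L/s, the probability that two visits differ is 2f(1−f). Averaged over f from 0 to 1 this is 2(1/2 − 1/3) = 1/3.

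**Size of the spurious change.** One slice is s/L of the level's volume. A change of ±s/L with probability 1/3 has SD = (s/L) × √(1/3) = 0.577 × s/L.

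| Unit | s, L (mm) | One slice | SD of spurious change |
|---|---|---|---|
| Single level | 3, 40 | 7.5% | 4.3% |
| Single level | 4, 35 | 11.4% | 6.6% |
| Single level | 5, 30 | 16.7% | 9.6% |
| L1–L5 total | 3, 190 | 1.6% | 0.9% |
| L1–L5 total | 5, 170 | 2.9% | 1.7% |

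A simulation with level heights varying between participants (SD 2 mm) agrees: counts differ in 32–34% of participant-levels, and the per-level SD is 4.3–9.6%.

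**If the scans are repositioned closely.** Let the grid shift between visits with an SD of 1 mm (mean absolute shift 0.80 mm). The probability of a differing count is about 2(0.80)/s − 2(1)/s². At s = 3 this is 0.533 − 0.222 = 0.311, and 7.5% × √0.311 = 4.2%. At s = 5 it is 0.32 − 0.08 = 0.24, and 16.7% × √0.24 = 8.2%. Careful positioning to within a millimetre or so therefore does not remove the effect on a single level.

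**Effect on power.** Suppose a true change of 5% or 10% with SD = change/0.73 (6.85% or 13.7%), and add noise e: d = change / √(SD² + e²).

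| Noise e | d | Paired power, n = 17 | Two-sample power, 17 per group |
|---|---|---|---|
| 0 | 0.73 | 81% | 54% |
| 0.9% (total) | 0.72–0.73 | 80–81% | 53–54% |
| 1.7% (total) | 0.71–0.72 | 78–80% | 52–54% |
| 4.5% (one level) | 0.61–0.69 | 66–77% | 41–50% |
| 8% (one level) | 0.48–0.63 | 45–68% | 27–43% |

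**What the division by length achieves.** If area varies linearly by ±20% about its mean within a level, the simulated noise SD is 4.4–9.8% for summed volume and 0.9–2.0% for mean cross-sectional area, about one fifth. At ±30% it is 4.5–10.0% against 1.3–2.9%.

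**The case against.** The strongest reply has four parts.

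*Slice spacing, stack alignment and border rules belong in an imaging manual, and an article may leave them out.* That is right, and their absence is not the point. The point concerns the stated choice of a per-level sum, which responds to slice count whatever the manual says unless the count is held equal.

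*The limits are anatomical landmarks, and a shifted stack that loses a slice at one end gains one at the other.* This largely stands for a pure one-slice shift, where only the difference between the two end areas remains; at an internal border the slice passes to the neighbouring level and mostly cancels in the total. A reader might infer that any one-slice shift shows up as growth or loss, but the measurement description does not support that. What is left is border rounding, which occurs even with perfectly identified landmarks.

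*The article does not say whether single levels or the L1–L5 total will be analysed, and for the total the loss is trivial.* This stands and limits the point to per-level analyses.

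*The comparison with area is one-sided.* This also stands. A single-slice area has its own positioning error, already contained in the 0.73 from the cited studies, and summing many slices averages over it. The article's remark that volume is more accurate than a single slice is not contradicted. The calculation above adds noise to 0.73 without crediting that averaging, so its power figures lean pessimistic.

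**Conclusion.** The point holds as a minor matter of precision. For size at a single level, slice-count rounding plausibly adds a spurious change with an SD of about 4–10% of that level's volume; for the L1–L5 total it is about 1–2% and can be ignored. These ranges rest on assumed spacing, level height and slice position, none of which the article gives.

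Three stronger readings are not supported:

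- That the trial's power falls to 45% (paired) or 27% (between groups). Those values need single-level analysis, 8% noise and a true change of only 5%, all assumed.
- That the result is biased. With 1:1 randomisation, and since "only the assessor will be blinded" (Blinding), the noise should be similar in both arms and favour neither.
- That the whole primary outcome is affected. The fat-signal fraction does not scale with the number of slices and is largely untouched.

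**What to change.** In the multifidus and erector spinae MRI sections, state that per-level size will be analysed as mean cross-sectional area for each level and side, that is, volume divided by (number of slices × slice spacing). Alternatively, state that the same number of slices per level will be used at both visits of a participant. Keep raw volume as a supportive measure. If only the L1–L5 total is to be analysed, saying so is enough.

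The cost is one sentence and one division on tracings already planned. No treatment signal is lost, because the bony length of a level does not change within a participant over 10 weeks. Mean area also puts the size outcome on the same kind of scale as the studies behind the 0.73.
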